## Abstract

**Introduction:**

Radiation Therapy and IRreversible Electroporation for Intermediate Risk Prostate Cancer (RTIRE) is a phase II clinical trial testing combination of radiation therapy and irreversible electroporation for intermediate risk prostate cancer

**Background:**

PCa is the most common non-cutaneous cancer in men and the second leading cause of cancer death in men. PCa treatment is associated with long term side effects including urinary, sexual, and bowel dysfunction. Management of PCa is based on risk stratification to prevent its overtreatment and associated treatment-related toxicity. There is increasing interest in novel treatment strategies, such as focal therapy, to minimize treatment associated morbidity. Focal therapy alone has yet to be included in mainstream guidelines, given ongoing concerns with potentially higher risk of recurrence. We hypothesize combining focal therapy with whole gland, reduced dose radiotherapy will provide acceptable oncologic efficacy with minimal treatment associated morbidity. RTIRE is a phase II single institution, investigator-initiated study combining a local ablative technique though local irreversible electroporation (IRE) with MR guided RT (MRgRT) to treat the entire prostate. The goal is to provide excellent oncologic outcomes and minimize treatment related side effects through leveraging benefits of locally ablative therapy with established radiation treatment techniques.

**Methods:**

A total of 42 men with intermediate risk PCa per NCCN guidelines and focal grade group (GG) 2 or 3, Gleason Score (GS) 3 + 4 or GS 4 + 3, cancer in an MRI target will be enrolled. Patients with MRI visible foci of GG2/GG3 will undergo focal therapy with IRE of this lesion. Following successful focal therapy, patients will then undergo a course of reduced dose, whole gland MRgRT with either 32.5 Gy in 5 Fractions or 22 Gy in 2 fractions. The primary objective of the study is to determine safety. Secondary outcomes include evaluation of oncologic efficacy (as measured by the proportion of patients free of clinically significant cancer as defined as > Grade Group 1 at 1-year follow-up biopsy), imaging characteristics of patients pre and post RTIRE, impact on quality of life (QoL), and PSA kinetics.

**Discussion:**

Combining IRE with a reduced dose radiotherapy may offer a new treatment paradigm for PCa by both reducing treatment effects of full dose radiotherapy and minimizing the risk of recurrence observed with focal therapy.

**Trial Registration:**

Clinicaltrials.gov identifier: NCT05345444. Date of registration: April 25, 2022. Protocol Version: 6.0, July 7, 2023.

**Supplementary Information:**

The online version contains supplementary material available at 10.1186/s12894-024-01506-8.

## Background

PCa is the most common non-cutaneous cancer in men and the second leading cause of cancer death in men. In the US in 2023, PCa is estimated to account for 29% of new cancer diagnoses and 11% of cancer related deaths [1]. The current treatment paradigm for men with newly diagnosed prostate typically begins with initial disease risk stratification based on a multitude of factors specific to the patient and their cancer. A commonly employed stratification framework is published in National Comprehensive Cancer Network PCa guidelines. Recommendations regarding additional work up and definitive treatment recommendations are based on disease risk in the context of predicted life expectancy. Initial risk ranges from very low to high risk depending on stage, PSA as well as pathology from biopsy. Standard of care treatment options for men with favorable intermediate risk disease include active surveillance, radiotherapy or prostatectomy [2]. Individualized oncologic treatment takes into account patient factors, expected outcomes from the aforementioned treatment strategies while balancing risks, benefits and expected acute/ long term side effects and tailoring recommendations through shared decision-making process.

Low risk PCa patients, who are unlikely to benefit from treatment, as treatment does not outweigh treated associated toxicity or risks, are placed on active surveillance (AS). AS consists of repeat laboratory analysis, imaging, and prostate biopsy at variable intervals. Patients with localized intermediate or high-risk PCa are offered definitive treatment: surgery or radiation therapy. Thus, PCa patients with low risk or clinically insignificant PCa do not need treatment whereas those with intermediate/high risk PCa or csPCa do need treatment [3]. Unfortunately, both surgery and radiation therapy are not without significant treatment-related toxicity including sexual and urinary dysfunction – which impacts not only PCa patients but also their partners. There is significant interest among physicians and patients for treatment options that minimize these side effects, but also deliver definitive cancer treatment, i.e., focal therapy [4].

## Methods/Design

This is a single site phase II trial for subjects with intermediate risk PCa with a focal GG2 or GG3 lesion with MRI target who will undergo IRE followed by SBRT with workflow shown in Fig. 1. We hypothesize that the combined therapy will be feasible and safe to perform with low morbidity and enhanced oncologic efficacy. The initial feasibility study (*N* = 10) is to determine the ability to perform IRE followed by SBRT. The primary endpoint is feasibility which is defined at 80% of subjects (8 subjects) assessed at 12-week post-IRE/6 weeks post-SBRT within 1 year from first subject enrollment. If the feasibility is met, the trial will then accrue an additional 32 patients for inclusion in the phase II trial.

**Fig. 1 Fig1:**
[figure not shown]
Treatment Workflow

The phase II component has a safety run-in cohort of patients. The first 10 patients after the feasibility portion will be treated with 2 fractions of RT. If at the 3-month follow-up, 3 or more patients have reported a grade 3 or higher AE, the 2-fraction schedule for RT will be deemed not tolerable and the remaining patients (*N* = 22) will be treated with the 5 fraction of RT schedule. All patients (*N* = 10 feasibility, *N* = 10 safety run-in, and *N* = 22) will be evaluable for the Phase II component. The general trial schema for the feasibility and phase II portion of the study are shown in Fig. 2. The co-primary endpoints are safety and oncologic efficacy evaluated as the proportion of patients who remain csPCa-free (> Grade Group 1) at the one-year follow-up. Note that this will be determined by the number of patients who are csPCA free divided by the total number of patients. If a patient does not have a one-year follow-up, they will be classified as a failure (i.e., are not cancer free). Additionally, patients with GG1 disease on 12-month post treatment biopsy will not be classified as a failure.

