## Patient selection, study enrollment, and randomization and blinding

Subjects ≥ 18 years of age with a new diagnosis of intermediate risk PCa and a focal GG2 or GG3 lesion in MRI target who meet the full inclusion and exclusion criteria will be notified of their eligibility for participation in this clinical trial. Subjects who agree to participate in the trial will sign the approved informed consent form and will be provided with a copy of the signed document. Subjects will be registered within the Weill Research Gateway-Clinical Trials as per the standard operating procedure for Subject Registration. Subjects will then undergo a screening visit to ensure all aspects of screening are complete as shown in Table 1.

**Table 1 Tab1:** Schedule of Trial Events

Study Procedures	Screening	IRE	Post-IRE 1-2wk FUP	Last Day RT	3,6,9-mo FUP	12-mo FUP	24-mo FUP
Informed Consent	X						
Demographics/ MH	X						
Physical Exam	X		X	X	X	X	X
VS, Height, weight	X		X	X	X	X	X
PSA	X				X	X	X
Pelvic MRI	X*					X	
PSMA PET	X*					X	
EPIC-CP	X			X	X	X	X
IPSS	X			X	X	X	X
IIEF-5	X			X	X	X	X
Tissue Biopsy (Research)		X					
Research samples (Blood, Urine)	X			X		X	
Adverse Events (CTCAE v5.0)	X	X	X	X	X	X	X
Post-Treatment Biopsy (+/- 1 month)	X					X	

*Imaging completed ≤ 9 months acceptable for enrollment

IRE Irreversible electroporation, FUP follow up visit, mo months, MH medical history, PSMA PET prostate-specific membrane antigen positron emission tomography, EPIC-CP Expanded PCa Index Composite for Clinical Practice, IPSS International Prostate Symptom Score, CTCAE v5.0 Common Terminology Criteria for Adverse Events version 5.0

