### Radiotherapy

After consent, eligibility verification, and IRE patients will undergo CT/MRI simulation and radiotherapy planning. Patients will receive treatment to the prostate + seminal vesicles to a dose of 32.5 Gy in 5 fractions or 22 Gy in 2 fractions. The rationale behind the selected dose relates to an estimated a/b ratio of 2.7 for PCa supported by ultra-hypofractionation trials and a large meta-analysis [5, 6]. With a lower α/β value, PCa should have an improved therapeutic ratio with ultra-hypofractionation. Furthermore, if the α/β formalism and assumed values for PCa are correct and one maintains a constant biologically effective dose for normal tissues, there is the potential for increased tumor control with ultra-hypofractionation in this setting. The dose selected for this trial is less than the therapeutic dose when radiation alone is used for intact PCa (7–8 Gy x 5 fractions or 12.5–14 Gy x 2 fractions) but has a biological effective dose of > 100 Gy based on the α/β value of 2.7 Gy.

Full details regarding radiation therapy treatment planning/simulation set-up, contouring, PTV and OAR prescription dose constraints, adaptive MR-Linac planning can be found in Supplemental File 1.

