Patient reported side effects were also reviewed as part of the ProtecT clinical trial and men treated with RT tend to have worse GI toxicities compared to those treated with RP with reports of 1 in 8 men experiencing long term toxicity. Recent trials examining late toxicities in patients undergoing stereotactic body radiotherapy (SBRT) with modern techniques suggest approximately 10% of patients may experience long term grade ≥ 2 GI toxicities and 0.4% grade ≥ 3 toxicities [10–12]. The recently published MIRAGE trial evaluated physican reported toxicities and patient reported symptoms for patients randomized to either MR-guided vs. CT-guided SBRT [13]. The results of the trial suggest that reduced treatment margin and lack of fiducial placement, allowed by intra-fraction MRI imaging for patients treated with MR-Linac, significantly reduced acute GI and GU toxic side effects compared to patients treated with CT guided radiotherapy. Grade ≥2 GU toxic effects were reported in 43.4% vs. 24.4% of patients treated with CT vs. MRI guided SBRT, respectively. There was no grade ≥ 2 GI toxic effects reported in patients treated with MRI guidance compared to 10% of patients undergoing SBRT with CT guidance. While there are some caveats regarding the interpretation and extrapolation of the results for this study as it relates to MRI vs. CT based SBRT, it serves as an excellent benchmark regarding acute toxicities and side effects in patients treated with modern SBRT techniques.

IRE is a local, minimally invasive ablative technique which uses physical placement of probes into the prostate tissue allowing for the application of pulsatile electrical currents to a focal target area to treat malignant tissue. These electrical currents lead to cell membrane destabilization causing alteration of the membrane shape and formation of nanopores which ultimately leads to irreversible damage and apoptosis through disruption of cellular osmotic balance [14]. The technique has been studied extensively in both animal models and in human subjects with promising oncologic and functional outcomes observed and well summarized in a review article by Ong et al. [15]. 

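### As worded, the run-in rule still gives 2 fractions to a run-in patient who has not started RT after a third grade 3+ patient has settled that the schedule is rejected (minor)

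*Protocol article*

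**What the plan says.** All of this is in the protocol article.

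- **Methods/Design, run-in paragraph below Fig. 1.** The assignment carries no condition: "The first 10 patients after the feasibility portion will be treated with 2 fractions of RT". The rule follows: "If at the 3-month follow-up, 3 or more patients have reported a grade 3 or higher AE, the 2-fraction schedule" "will be deemed not tolerable and the remaining patients", given as N = 22, move to 5 fractions.
- **Same paragraph and Sample size and accrual.** The total is 10 feasibility + 10 run-in + 22 = 42, so the 22 contains no run-in patient.
- **Irreversible electroporation.** RT planning begins no sooner than 6 weeks after IRE. A run-in patient can therefore be enrolled and ablated but not yet irradiated.
- **Adverse events.** AEs are graded at scheduled and unscheduled time points and logged. Table 1 has an AE check on the last day of RT, and the next scheduled one is at 3 months.
- **Data management and safety monitoring.** An institutional data safety monitoring board is the central monitoring body. No rule for the run-in is given there.

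**The concern.** The rule states its threshold, its timing and the patients it affects, and these do not fit together. The threshold is a count of patients who have had a grade 3+ AE, and on the natural cumulative reading that count only rises. In a fixed cohort of ten, the third case decides the verdict whatever happens to the others. The consequence is tied to the 22 patients after the run-in, so the wording leaves a run-in patient who has not started RT on 2 fractions.

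That patient would receive a schedule the trial's own criterion has already rejected, while the 5-fraction schedule is available in the same protocol. His outcome could not change the decision. What is at stake is avoidable exposure of a small number of men. The efficacy test is not involved.

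**Working it through.** **The plan's own figure.** Sample size and accrual gives 94.3% power for N = 42, 0.80 against 0.95, one-sided 10%. The smallest rejection count with exact alpha at or below 0.10 is 38 of 42: alpha 0.058, power 0.943. The figure reproduces, and nothing below touches it. The article gives no operating characteristics for the run-in rule.

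**Inputs for the run-in.** Ten patients and a threshold of 3 come from Methods/Design. Three inputs are not in the document and are assumed:

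- *True grade 3+ rate p:* 5% to 40%. The Discussion's benchmarks are other quantities: long-term toxicity after SBRT ("GI toxicities and 0.4% grade" 3 or higher) and grade 2 or higher events in a randomised comparison ("GU toxic effects were reported in 43.4% vs. 24.4% of patients treated with CT vs. MRI guided SBRT"). The Radiotherapy section adds that the dose is "less than the therapeutic dose when radiation alone is used for intact PCa". These make the low end of the range relevant.
- *Pace:* one or two RT starts per month. The feasibility target is 8 patients "assessed at 12-week post-IRE/6 weeks post-SBRT within 1 year from first subject enrollment". That leaves 12 − 2.8 = 9.2 months, and 8/9.2 = 0.87 IREs per month. This is a floor for the feasibility stage and does not forecast phase II pace.
- *When an AE becomes known:* either evenly over the 3 months after RT, or only at 3 months.

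**Step 1, how often the rule triggers.** P(at least 3 of 10) under Binomial(10, p); see the table.

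**Step 2, AEs known only at 3 months.** The third affected patient is number k with probability P(k) = C(k−1, 2) p³ (1−p)^(k−3). At one start per month, three more men start by the time his AE is known, so 10 − k − 3 = 7 − k men are left, and the mean is Σ (7−k) P(k) for k = 3 to 6. At p = 0.30: 4(0.0270) + 3(0.0567) + 2(0.0794) + 1(0.0926) = 0.53. At two starts per month six more men start, only k = 3 leaves anyone, and the mean is p³.

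**Step 3, AEs spread evenly over 3 months.** Simulation: ten starts at fixed gaps, event indicator Bernoulli(p), event time uniform on 0 to 3 months after RT. Starts strictly after the third event are counted.

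Mean number of run-in men starting 2 fractions after the third event, over all trials:

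| True rate | P(trigger) | Even spread, 1/month | Even spread, 2/month | Known at 3 months, 1/month | Known at 3 months, 2/month |
|---|---|---|---|---|---|
| 5% | 0.012 | 0.014 | 0.007 | 0.004 | 0.0001 |
| 10% | 0.070 | 0.10 | 0.05 | 0.03 | 0.001 |
| 20% | 0.322 | 0.56 | 0.29 | 0.19 | 0.008 |
| 30% | 0.617 | 1.35 | 0.74 | 0.53 | 0.027 |
| 40% | 0.833 | 2.30 | 1.35 | 1.02 | 0.064 |

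**Step 4, given a trigger.** With even spread and one start per month, dividing by P(trigger) gives about 1.7, 2.2 and 2.8 men at 20%, 30% and 40%. The number who receive 2 fractions under an early stop is then on average 10 − 1.7 = 8.3, 10 − 2.2 = 7.8 and 10 − 2.8 = 7.2.

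**Upper bound.** If each man's AE were known before the next man started, the means over all trials would be 0.02, 0.15, 0.80, 1.87 and 3.05 at 5% to 40%.

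**The case against.** The strongest reply is that this is a condensed article. It states a planned cohort and a planned read, and what happens if the threshold is reached early is run-in conduct that the full protocol may cover. That document is not shown. The institutional review board receives all AEs, and a monitoring board oversees the trial. The harm would need both, and the investigators, to stay passive after three grade 3+ patients among ten. A fixed cohort of ten with one read is also a legitimate simple design.

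Much of this stands. A reader might infer that run-in patients will in fact be irradiated on a rejected schedule, or that the trial has no early stop. The document supports neither inference. It supports only the statement about the rule as worded: an unconditional assignment of ten and a switch fixed to 22. General oversight does not alter that wording.

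The reply on size also stands. A reader might take two to three men as the expected exposure. That figure needs a 20% to 40% grade 3+ rate, slow accrual, early knowledge of AEs and conditioning on a trigger, and nothing in the document supports a rate that high. Table 1 schedules no AE visit between the last day of RT and 3 months. Unscheduled grading would bring some events forward, so the truth lies between the two lag scenarios, but the document does not say where.

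**Conclusion.** The gap in the wording is real on the cumulative reading of the rule. If only AEs still present at the 3-month visit counted, certainty would come later. It is a minor point: no stated figure is wrong, and sample size, alpha and power are unaffected.

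The expected benefit of closing the gap is about 0.1 patient or less at a true grade 3+ rate of 10% or below, under either lag. It is almost nil at any rate up to 40% if AEs are known only at 3 months and two men start per month. It reaches roughly half a patient to just over two patients at 20% to 40% with one start per month and events spread evenly. That last setting is the one a run-in rule exists to guard against, which is why a single sentence is worth adding. Rate, pace and lag are all assumptions.

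**What to change.** Add to the run-in paragraph:

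> If a third run-in patient treated with 2 fractions has a grade 3 or higher AE before the 3-month read, the 2-fraction schedule is deemed not tolerable at that point and every patient who has not started RT, including any left in the run-in, receives 5 fractions; otherwise the rule is read as planned.

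Limiting the early trigger to men treated with 2 fractions prevents rejection of the schedule on men who had only IRE. This is narrower than the present wording, which counts patients with any grade 3+ AE, so it should be a deliberate choice. Provided all ten would otherwise start RT, the probability of each verdict is unchanged.

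**Cost.** One sentence and a running count, which the existing AE log can supply. No extra visits, patients or accrual hold are needed.

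**Downsides.** A man already planned for 2 fractions needs a new plan. Fewer than ten men supply 2-fraction data when the rule fires early. The observed 2-fraction toxicity proportion is then biased upward, because recruitment to the schedule ends on an event, and it should be reported as coming from a stopped cohort.

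If the full protocol already has such a stop, it is enough to state it in the article's rule.

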**Fig. 2 Fig2:**
[figure not shown]
Trial Schema

Secondary objectives will include determining short-term post-treatment safety profile, oncologic efficacy of RTIRE at 12 months. Determine the impact of RTIRE on health-related quality of life (HRQOL), post-RTIRE treatment prostate-specific antigen (PSA) kinetics including time to PSA nadir and post-nadir PSA stability, assess the effectiveness of therapy by post-treatment multiparametric magnetic resonance imaging (mpMRI) to evaluate the area of necrosis and presence of residual tissue, assess the effectiveness of therapy by recording the rates of biochemical and clinical progression and the need for secondary or adjuvant treatment following therapy. A full list of primary, secondary, and exploratory objectives as well as full inclusion and exclusion criteria are available in the attached supplemental file or on the corresponding trial page found on clinicaltrials.gov website.

## Patient selection, study enrollment, and randomization and blinding

Subjects ≥ 18 years of age with a new diagnosis of intermediate risk PCa and a focal GG2 or GG3 lesion in MRI target who meet the full inclusion and exclusion criteria will be notified of their eligibility for participation in this clinical trial. Subjects who agree to participate in the trial will sign the approved informed consent form and will be provided with a copy of the signed document. Subjects will be registered within the Weill Research Gateway-Clinical Trials as per the standard operating procedure for Subject Registration. Subjects will then undergo a screening visit to ensure all aspects of screening are complete as shown in Table 1.

**Table 1 Tab1:** Schedule of Trial Events

Study Procedures	Screening	IRE	Post-IRE 1-2wk FUP	Last Day RT	3,6,9-mo FUP	12-mo FUP	24-mo FUP
Informed Consent	X						
Demographics/ MH	X						
Physical Exam	X		X	X	X	X	X
VS, Height, weight	X		X	X	X	X	X
PSA	X				X	X	X
Pelvic MRI	X*					X	
PSMA PET	X*					X	
EPIC-CP	X			X	X	X	X
IPSS	X			X	X	X	X
IIEF-5	X			X	X	X	X
Tissue Biopsy (Research)		X					
Research samples (Blood, Urine)	X			X		X	
Adverse Events (CTCAE v5.0)	X	X	X	X	X	X	X
Post-Treatment Biopsy (+/- 1 month)	X					X	

*Imaging completed ≤ 9 months acceptable for enrollment

IRE Irreversible electroporation, FUP follow up visit, mo months, MH medical history, PSMA PET prostate-specific membrane antigen positron emission tomography, EPIC-CP Expanded PCa Index Composite for Clinical Practice, IPSS International Prostate Symptom Score, CTCAE v5.0 Common Terminology Criteria for Adverse Events version 5.0

All subjects will undergo a transperineal 14-core template biopsy using UroNav’s ultrasound/MRI fusion technology to confirm outside diagnosis and/or establish eligibility wherein patients have 1 identified area of csPCa with acceptance of non csPCa in other cores. Additional targeted biopsies of lesions seen on mpMRI or PSMA-PET/CT will also be performed but patients at minimum will have a baseline 14-core systematic biopsy at baseline. Patients must have pelvic MRI and PSMA PET-CT within 9 months of enrollment on the study and will have updated H&P including full medical history, vital signs, PSA, as well as baseline EPIC-CP, IPSS and IIEF-5 questionnaire completed at screening visit. Blood and urine samples taken at the initial screening visit will be collected as well. Patients will be scheduled for their outpatient IRE procedure at a suitable future scheduled date. There will be no randomization performed after enrollment and neither clinicians, subjects nor data analyzers blinded to the assigned treatment.

